**Nature and extent of the burden and risks associated with participation, benefit and group relatedness:** Currently epidermolysis bullosa patients are using cannabinoid-based medicines both with and without medical supervision. Participants are 16 years or older and mentally competent. They will receive the study intervention Transvamix-oil, a compounded medication (*magistrale bereiding*) readily available on prescription and is currently used by patients for various medical indications in the Netherlands. Transvamix-oil can produce side effects that can be discomforting, but are mild, well tolerated, and disappear within 4-8 hours after administration upon which the following dose can be reduced to mitigate the recurrence of side-effects. Participants will undergo 3x 30 minute MRI scans. A daily logbook will be completed at home electronically - pertaining to the dose administered, possible side-effects and pain/pruritus scores. All participant reported outcomes are completed electronically at home.

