### **2.3 Secondary Objectives**

- To explore the effect of Transvamix, relative to placebo, on participant reported general pain quality scores, and pain intensity, in EB patients with chronic pain.
- To explore the effect of Transvamix, relative to placebo, on pain self-efficacy in EB patients with chronic pain.
- To explore the effect of Transvamix, relative to placebo on pruritus intensity in EB patients with chronic pain.
- To explore the effect of Transvamix, relative to placebo on brain connectivity in areas corresponding to the affective pain modulation circuit.
- To determine the sub-side effect threshold maintenance dose achieved during titration of Transvamix and placebo.
- To determine the frequency and participant-reported burden of adverse-events encountered during titration of Transvamix and placebo.

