## 6.6 Dosages, dosage modifications and method of administration

Transvamic and placebo are administered sublingually using a 1 millilitre dosing syringe. All participants will follow the predetermined titration scheme (*Table 2*). The titration will be stopped at the onset of side-effects (as reported by the participant), and the dose administered reduced by one day in the titration scheme. This will be called the sub-side effect threshold maintenance dose.

This achieved dose will be maintained for the remaining intervention period until day 14 is completed for each intervention (Transvamic and placebo). Both placebo and IMP (Transvamic) will undergo the same titration scheme.

The maximum dose is 0.75ml/day Transvamic or placebo (divided between 4 separate administrations).

For additional information please see *D1\_Investigators Brochure* chapter 5.3.1.

| Table 2: Titration Scheme                                 |           |          |           |            | Total   | Total THC | Total CBD |
|------------------------------------------------------------------|-----------|----------|-----------|------------|---------|-----------|-----------|
| Transvamic (100mg/mL THC & 50mg/mL CBD) & Placebo |           |          |           |            | (ml)    | (mg)      | (mg)      |
| Day                                                              | 6AM – 9AM | 11AM-2PM | 4PM – 7PM | 9PM – 12AM |         |           |           |
| 1                                                                | -         | -        | -         | 0,05 ml    | 0,05 ml | 5         | 2,5       |
| 2                                                                | -         | -        | -         | 0,05 ml    | 0,05 ml | 5         | 2,5       |
| 3                                                                | 0,05 ml   | -        | -         | 0,05 ml    | 0,1 ml  | 10        | 5         |
| 4                                                                | 0,05 ml   | -        | 0,05 ml   | 0,05 ml    | 0,15 ml | 15        | 7,5       |

|    |         |         |         |         |         |    |      |
|----|---------|---------|---------|---------|---------|----|------|
| 5  | 0,05 ml | 0,05 ml | 0,05 ml | 0,05 ml | 0,2 ml  | 20 | 10   |
| 6  | 0,05 ml | 0,05 ml | 0,05 ml | 0,1 ml  | 0,25 ml | 25 | 12,5 |
| 7  | 0,1 ml  | 0,05 ml | 0,05 ml | 0,1 ml  | 0,3 ml  | 30 | 15   |
| 8  | 0,1 ml  | 0,05 ml | 0,1 ml  | 0,1 ml  | 0,35 ml | 35 | 17,5 |

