#### 8.1.2 Secondary study parameters/endpoints.

- The difference of mean scores of pain qualities between Transvamic and placebo.  
*Will be measured as the difference of the mean of all SF-MPQ2 pain quality items (which have received a score >0 on NRS) between Transvamic and Placebo.*
- The difference of mean scores of pain intensity between Transvamic and placebo.  
*Will be measured as daily changes in pain intensity (1-14 days placebo, 1-14 days Transvamic) using the VAS-Pain ([no pain] 0-100 [worst pain imaginable] unit scale) for pain intensity. The change score (delta) from baseline to Transvamic (day 14) and Placebo (day 14) will be calculated.*
- To determine the effect of Transvamic on pain self-efficacy  
*Will be measured using the PSEQ survey pre-intervention (1x baseline) and during intervention (1x Transvamic, 1x placebo), a 10-item survey on the ability to continue normal life given ongoing pain.*
- The difference of mean scores of pruritus intensity between Transvamic and placebo.  
*Will be measured as daily changes in pruritus intensity (1-14 days placebo, 1-14 days Transvamic) using the VAS-Pruritus ([no pruritus] 0-100 [worst pruritus imaginable] unit scale) for pruritus intensity. The change score (delta) from baseline to Transvamic (day 14) and Placebo (day 14) will be calculated.*
- The difference in brain connectivity of the seed regions (anterior cingulate cortex and amygdala) to the brain cortex between Transvamic and placebo.  
*Will be measured using voxel-based analysis of blood oxygen-level dependent functional magnetic resonance imaging (fMRI-BOLD).*

- To determine sub-side effect threshold maintenance dose achieved of Transvamic during titration and the respective interindividual variability (CV%).  
*Will be measured as the dose administered on day 14 of placebo and Transvamic interventions. CV% is measured as inter-participant variance of dose achieved on day 14 of placebo and Transvamic interventions.*
- To inventorize how many and which participant-experienced adverse-events during titration and maintenance of Transvamic and the patient reported burden for each adverse event on numeric rating scale (NRS [not burdensome at all] 0-10 [extremely burdensome]).

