#### 10.2.2 Dose achieved

Descriptive statistics will be employed to portray means, medians, coefficient of variation (CV%) and standard deviations of achieved doses for the entire cohort. No sub-group analyses will be performed on dose-achieved. The dose achieved, is the dose administered by the participant during the sub-side effect threshold maintenance period – as seen on day 14 and 42 of the study.

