doses required for experienced side effects from either CBD or THC in TransvamiX-oil. The possible acute onset side effects, such as dizziness or an increased appetite are short lasting (1-2 hours, and completely withdrawn 4-8 hours after administration) and can be avoided by reducing the following dose administered to the previous step in the titration scheme. In case of accidental overdose, patients are advised to go to a quiet area and just wait until the adverse effects wear off. In case of emergencies patients will have access to adequate medical support.

k. Why are both THC and CBD present in the study medication?

Clinical studies have shown that the combination of THC and CBD are superior to either cannabinoid alone. Additional CBD has been shown to reduce the unwanted side effects of THC administration through receptor antagonism, making the combination more preferable to patients receiving CBM treatments .

l. Are cannabinoid-based medicines addictive?

The key component responsible for the psychotropic effects and dependence potential of cannabinoid-based drugs is THC, acting on pathways in the central nervous system. Substance abuse can have both physical and psychological influences. Dependence is preceded by an increased tolerance to the drug and negative withdrawal symptoms, followed by psychosocial consequences.

To address the former, a review of a CBM (comprising THC and CBD) in 2011 with >1500 patient-years of treatment experience showed the absence of increased tolerance to the study drugs – i.e. the dose remained the same throughout the studies or even was reduced . Dutch data on the number of CBM prescriptions show an unchanged duration of use (first dispensation to last dispensation) between 2003-2011 and 2012-2016, and the average daily administration remaining remarkably stable .

The abuse potential of CBMs comprising THC however cannot be directly compared with commercial THC preparations as the underlying motivation to administer the drug in disease is to relieve symptoms in the absence of side-effects. In addition to this the administration form used most often recreationally, with a higher risk for abuse, is intrapulmonary, with higher percentages of active THC, leading to fast onset and high plasma peaks, and an increased chance for withdrawal symptoms . This is not the case in current regulated CBMs following dose-titration schemes with supervision.

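### The day-14 dose does not always equal the sub-side effect threshold maintenance dose: it is too high for onset on day 14, not below the threshold for onset on day 2, and only a lower bound with no onset

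*Protocol*

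**What the plan says.** Section 2.3 lists as a secondary objective: "To determine the sub-side effect threshold maintenance dose achieved during titration of Transvamix and placebo".

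Section 6.6 sets the dosing rule. Titration stops when the participant reports a side effect, "and the dose administered reduced by one day in the titration scheme", and the result is named the maintenance dose. Then: "This achieved dose will be maintained for the remaining intervention period until day 14 is completed for each intervention". The cap is 0.75 ml per day. Table 2 reaches the cap only on day 14, and days 1 and 2 carry the same dose.

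Section 8.1.2 fixes the measurement: "Will be measured as the dose administered on day 14 of placebo and Transvamic interventions". It calculates the CV% on the same quantity. Section 10.2.2 takes the dose during the maintenance period, "as seen on day 14 and 42 of the study", and plans "means, medians, coefficient of variation (CV%) and standard deviations of achieved doses for the entire cohort". Study day 42 is the 14th day of the second period (42 − 29 + 1 = 14), so the two sections agree with each other.

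Two other places describe dose reduction. The Summary says that "the following dose can be reduced to mitigate the recurrence of side-effects". Section 13.1(j) says that side effects "can be avoided by reducing the following dose administered to the previous step in the titration scheme".

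**The concern.** The endpoint is meant to show the highest step a participant can take without side effects. The protocol defines that step by going back from the onset day, but measures it by reading the dose on a fixed calendar day. The two match only if there is a lower step to go back to and at least one day left to take it. Table 2 fails the first condition at its start, where days 1 and 2 are identical, and the second at its end, where escalation continues through the measurement day.

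At stake is the reading of a listed secondary objective for both treatments. At the top of the scale one recorded number stands for different tolerability outcomes, and the same holds at the bottom. The mean, SD and CV% then mix doses that were tolerated, doses that were not, and doses limited by the cap. Section 10.2.3 also names the maintenance dose as a possible correlate of the fMRI changes, so the same values would enter that exploratory analysis.

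**Working it through.** **Inputs.** The four daily volumes per row of Table 2; 100 mg/mL THC; the 6.6 rule; the day-14 reading in 8.1.2 and 10.2.2.

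**Step 1: reproduce Table 2.** Daily THC = (sum of the four volumes) × 100. Days 1 to 14 give 5, 5, 10, 15, 20, 25, 30, 35, 40, 45, 50, 55, 65, 75 mg. All 14 totals agree with the protocol. Call these T(1) to T(14).

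**Step 2: apply 6.6.** For onset on day d, the maintenance dose is T(d − 1), held to the end of day 14.

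| First side effect | Scheduled dose that day (mg) | 6.6 dose (mg) | Recorded on day 14 (mg) | Result |
|---|---|---|---|---|
| Day 1 | 5 | no earlier row | not fixed | undefined |
| Day 2 | 5 | 5 | 5 | agree, but not below the onset dose |
| Days 3–13 | 10 to 65 | 5 to 55 | 5 to 55 | agree, and below the onset dose |
| Day 14 | 75 | 65 | 70 or 75 | disagree |
| None | – | threshold not reached | 75 | valid dose achieved; lower bound on threshold |

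**Step 3: onset on day 14.** Day-14 volumes are 0.20, 0.15, 0.20, 0.20 ml; day-13 volumes are 0.15, 0.15, 0.15, 0.20 ml. Suppose the remaining doses of that day drop to the day-13 level.

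- Onset after the first or second dose: 0.20 + 0.15 + 0.15 + 0.20 = 0.70 ml = 70 mg (70/65 = +7.7%).
- Onset after the third or fourth dose: 0.20 + 0.15 + 0.20 + 0.20 = 0.75 ml = 75 mg (75/65 = +15.4%).

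If nothing is reduced that day, the total is 75 mg. No onset day leads to a recorded 65 mg.

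**Step 4: effect on the mean.** One such participant among 16 shifts the mean by 5/16 = 0.3 mg to 10/16 = 0.6 mg.

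**Step 5: what a recorded value can mean.** 5 mg arises from onset on day 2 (not tolerated) or day 3 (tolerated). 75 mg arises from late onset on day 14 (not tolerated) or from no onset (tolerated).

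**Step 6: effect of the cap on CV%.** The protocol does not give the share reaching 75 mg. As an illustration, assume all other participants have onset spread evenly over days 3 to 13. Their doses are then 5, 10, …, 55 mg, with mean 30 and variance 250. With share f at 75 mg, mean = 75f + 30(1 − f) and variance = 75²f + (30² + 250)(1 − f) − mean².

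| Share at 75 mg | Mean (mg) | CV% |
|---|---|---|
| 0 | 30.0 | 52.7 |
| 0.25 | 41.2 | 57.7 |
| 0.50 | 52.5 | 47.9 |
| 0.75 | 63.8 | 33.0 |
| 1 | 75.0 | 0 |

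CV% thus depends on how many participants reach the cap, and falls to zero if all do.

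**The case against.** The strongest reply is that the protocol asks only for the dose achieved. Section 2.3 speaks of the dose achieved during titration, 8.1.2 calculates CV% on the dose achieved on day 14, and 10.2.2 is headed accordingly. On that reading 75 mg with no side effect is the right entry, and a CV of 0% with everyone at the cap is a correct description. This stands. A reader might infer that the no-onset value is an error, but the documents do not support that. It is a valid dose achieved that should not be read as the side-effect threshold.

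A reader might also infer that 6.6 and the day-14 reading contradict each other for onset on days 1 and 2. For day 2 they agree: one day back is 5 mg and 5 mg is recorded. The fault is that the name does not fit, because 5 mg produced the side effect. For day 1 the protocol does not say that the participant stays on 5 mg. Going back one day could equally mean no dose, and 6.6 refers to Investigator's Brochure 5.3.1, which is not shown and may give an instruction. A claim of nearly two weeks on an offending dose is therefore not established.

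The logbook (8.3.1) records the titration day completed and the side effects, so tolerated and not tolerated can be separated after the fact. That is true, and it is why the fix is cheap. But the endpoint as defined in 8.1.2 and 10.2.2 does not use that information. Those sections already fix the measurement rule, so the day-14 mismatch is not simply a detail left to the analysis plan.

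**Conclusion.** The point holds, at minor severity. The day-14 dose is the intended quantity for onset on days 3 to 13. It is 5 or 10 mg too high for onset on day 14. It is not below the side-effect level for onset on day 2, and the dose is undefined in the protocol as shown for onset on day 1. With no onset it is a correct dose achieved but only a lower bound on the threshold.

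The numerical error for day-14 onset is small and needs a first side effect on exactly the last day. The ambiguity at 5 mg and 75 mg matters more for interpretation, but its size is unknown because the documents do not give the shares at the floor and the cap. The CV% figures above rest on an assumed onset pattern. The cap would weigh most in the placebo period if side effects are rarer there, which is also an assumption.

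The endpoint is secondary and descriptive in a study labelled explorative. A reader might infer that the primary comparison or the sample size is compromised; neither uses this dose.

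**What to change.** In 8.1.2 and 10.2.2:

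- Derive the threshold dose from the logged onset day as the Table 2 row before onset, which gives 65 mg for onset on day 14. Report the dose actually taken on day 14/42 separately.
- Classify onset at 0.05 ml as below 5 mg / not tolerated.
- Report per treatment the number with onset at 0.05 ml and the number reaching 0.75 ml without side effects (75 mg or more).
- State that mean, SD and CV% describe the dose taken within the cap.

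In 6.6, state what a participant does after a side effect at 0.05 ml, or copy the instruction from Investigator's Brochure 5.3.1 if it is there. Whether to stop, skip or continue is a clinical decision.

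The cost is a few sentences and one small table. The titration day and side effects are already in the daily logbook, and Table 1 lists the dose administered there too, so no further data or participants are needed.

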To date, it has also been shown that neither the dose administered nor detected plasma levels of cannabinoids are good predictors of pain alleviation when treated with CBMs. The high inter-individual variability (CV%) is likely due to patient variations in BMI, enterohepatic circulation, degradation in the gut, previous cannabinoid exposure, the endogenous cannabinoid system (endocannabinoid system) compositions and differences in administration technique. Additionally, the subjective effects after cannabinoid administration do not appear to have a classic monophasic dose-response relationship. One such study observed that higher doses did not lead to improved effectiveness, versus lower doses, in oromucosal cannabinoid preparations (THC & CBD). Another study did however highlight dose-dependent effects on heart rate, after inhaling cannabis (THC), however this dose-dependent relationship was absent for the subjective effects associated with cannabinoid administration. A recent study using vaporised cannabinoids in chronic pain patients with fibromyalgia (Bedrocan: Bediol, Bedrolite, Bedrocan & placebo) clearly showed that after single administration, the subjective changes in evoked pressure pain had a temporal relationship with plasma cannabinoid levels after administration – however only single doses were used in this study. Therefore, the current best-practice is for patients administering CBMs to undergo dose-escalation titration following a premeditated dosage build-up scheme (e.g. administration 4x daily). In order to achieve an effective dose, patients continue titration until side-effects are reached, and subsequently reduce their dose by one step in the titration scheme (table 1), and subsequently maintain this dose. Methods for dose-escalation vary significantly between patients in clinical practice, which is why a fixed titration scheme should be employed for research studies. This feasibly standardizes the dose-escalation for all participants in clinical studies.

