### 6.5 Description and justification of route of administration and dosage

The choice of administration form for this study is via the sublingual oro-mucosal route. The lipid soluble cannabinoids administered in the form of an oil are readily absorbed through the mucosa into sublingual vessels. Pharmacokinetic studies have demonstrated the fast-onset plasma concentrations and ease-of-dosing of sublingually administered cannabinoids (tetrahydrocannabinol-THC & cannabidiol-CBD), compared to oral and intrapulmonary administration forms.

Although intrapulmonary administration (for example by way of vaporization) leads to faster peak plasma concentrations, the therapeutic effects are short-lived and the risk for side-effects is higher. Through the oral route (tablet/swallowed), due to its poor bio-availability and the hepatic first-pass metabolism, dosing is unpredictable with a higher inter-individual variability compared to sublingual and inhaled administration routes.

The current standard in both the clinical setting and research studies point to the need for step-wise dose titrations in patients receiving CBMs comprising THC and CBD. Patients administering TransvamiX and TransvamiX-like drugs, by way of the

sublingual/oromucosal route, perform a dose-escalation, following a premeditated titration scheme. The titration schemes used in clinical practice and research studies show variation in dose-escalation, the consensus however is to start with administration of the lowest dose possible, and escalate up to a maximum of 75mg THC per day, during 14 days. The scheme used in this study is designed by Felix Farma based on current recommendations for sublingually administered Transvamic-like drugs in the Netherlands.

In clinical practice this scheme is used as a reference for patients who may deviate from said doses, however for this study participants will adhere to the same dose-escalation scheme.

Taken together, the oromucosal route of administration appears to be the most patient-friendly which is supported by a recent Dutch study showing an epidemiologic preference for sublingual administration of CBMs versus oral and intrapulmonary.

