### 8.3.1 Daily participant logbook completed by participants.

Participants will complete a logbook consisting of 3 parts each day in the evening (table 1) throughout the study period during which the participant received either Transvamic or placebo:

- Visual analog scales for pain and pruritus (VAS [no pain] 0-100 [worst pain/pruritus imaginable] units). These will be completed in the evening. Participants will be asked to complete VAS pain/pruritus retrospectively about the same day, subdivided into 3 timepoints in the day (*morning, afternoon and evening [or now]*).  
The periods of completion are as follows: Firstly, for baseline measurements (day -8 to -1) followed by Transvamic and placebo interventions (days 1 - 14 and 29 – 42).

- The titration scheme will be visualised and a checkbox ticked by the participant indicating the day of titration that was completed.
- Side effects will be reported following a multiple choice list\*, and the burden of the noted side effect indicated using numeric rating scales (NRS [not burdensome] 0-10 [extremely burdensome])
- Use of breakthrough medication or changes in analgesic medication recorded by participant.

\* Multiple choice list of side effects are categorized (in Dutch):

1. High gevoel (een vrolijke opgewekte stemming die langzaam overgaat in een tevreden gevoel van kalmte en rust).
2. Loomheid
3. Honger
4. Intensere beleving van kleuren en/of geluiden
5. Verlies van gevoel voor tijd en/of plaats
6. Sombere en/of angstige stemming
7. Rusteloosheid en/of slapeloosheid
8. Waanvoorstellingen
9. Versnelde hartslag
10. Duizeligheid
11. Warm of koud gevoel in handen en voeten
12. Rode branderige ogen
13. Spierverslapping
14. Droge mond
15. Anders, namelijk.....

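### The one-day step-back in Protocol 6.6 cannot lower the dose for side effects starting on days 1-2 and can return the same dose on later days, yet the held dose is called sub-side-effect

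*Protocol*

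**What the plan says.** Protocol 6.6 puts every participant on the 14-day scheme in Table 2, with the same volumes for Transvamix and placebo. At the onset of participant-reported side effects titration stops "and the dose administered reduced by one day in the titration scheme". The protocol names the result the sub-side-effect threshold maintenance dose. "This achieved dose will be maintained for the remaining intervention period until day 14 is completed for each intervention" No zero dose, stopping rule or second step-down appears in the text. For further information 6.6 refers to Investigator's Brochure 5.3.1, which is not at hand.

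Other sections describe the same manoeuvre as a real reduction:
- Section 1.3: "patients continue titration until side-effects are reached, and subsequently reduce their dose by one step in the titration scheme".
- Summary, on burden and risks: "upon which the following dose can be reduced to mitigate the recurrence of side-effects".
- Section 13.1, item j: effects "can be avoided by reducing the following dose administered to the previous step in the titration scheme".

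Section 6.5 says that the consensus is to "start with administration of the lowest dose possible", which makes row 1 the floor of the scheme.

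The held dose is also an outcome. Section 2.3 lists it as a secondary objective, and 8.1.2 defines it: "Will be measured as the dose administered on day 14 of placebo and Transvamic interventions". Section 10.2.2 reports it as mean, median, standard deviation and CV%.

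**The concern.** A rule that names its result sub-side-effect should always land below the dose at which the effect appeared. Here it need not, for two reasons. The first two rows are the same and nothing lies below them. Also, the rule counts whole calendar rows, whereas side effects start at a point within a day, often before that day's increase has been taken.

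Two things are at stake. A participant may go on taking a dose that has just caused a side effect, although the Summary and 13.1 describe a reduction. And the day 14 and day 42 doses would mix values that are below the participant's threshold with values that are not, under one label, in a sample of 16.

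**Working it through.** **Inputs.** Table 2 in Protocol 6.6 gives four administration windows per day (morning, midday, afternoon, late evening) at 100 mg/mL THC.

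**Step 1: reproduce the table.** Daily THC = total ml x 100. This gives 5, 5, 10, 15, 20, 25, 30, 35, 40, 45, 50, 55, 65 and 75 mg for days 1 to 14. All match the printed totals.

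**Step 2: drop in the scheduled daily total on going back one row** (row d minus row d-1).
- Day 1: no earlier row.
- Day 2: 5 - 5 = 0 mg.
- Days 3 to 12: 5 mg each.
- Day 13: 65 - 55 = 10 mg. Day 14: 75 - 65 = 10 mg.

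Judged by row totals alone, the rule fails only on days 1 and 2. There the remaining exposure at the causing dose is 13 x 5 = 65 mg THC (onset after the day 1 dose) or 12 x 5 = 60 mg (onset after the day 2 dose).

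**Step 3: onset before that day's increase.** Row totals assume that the whole day was taken. Define the dose being taken at onset as the sum of the last four windows ending with the latest dose. This measure is mine; the protocol does not use it. On day 6 the only increase is in the late-evening window. After the day 6 afternoon dose the last four windows are 4 x 0.05 ml = 0.20 ml = 20 mg. Going back one row from day 6 gives row 5, also 4 x 0.05 ml = 20 mg. The reduction is 20 - 20 = 0.

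The same occurs wherever the day's first increase is not the morning dose:

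| Day | First increase | Onset after | Taken (mg) | Held (mg) |
|---|---|---|---|---|
| 4 | afternoon | morning | 10 | 10 |
| 5 | midday | morning | 15 | 15 |
| 6 | late evening | morning, midday, afternoon | 20 | 20 |
| 8 | afternoon | morning, midday | 30 | 30 |
| 9 | midday | morning | 35 | 35 |
| 10 | late evening | morning, midday, afternoon | 40 | 40 |
| 12 | afternoon | morning, midday | 50 | 50 |
| 13 | midday | morning | 55 | 55 |

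These are 14 positions in the schedule, not probabilities. On days 3, 7, 11 and 14 the morning dose is raised, so the problem does not arise once that dose has been taken.

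**Step 4: evening dose, effect noticed the next day.** Section 1.2 puts peak THC at 2-3 hours after oromucosal absorption, so a dose taken between 9PM and midnight can peak after midnight. If the day 6 evening dose (0.10 ml) causes an effect that is counted as day 7 onset, one row back from day 7 is row 6: 25 mg held at 25 mg, with the 0.10 ml evening dose kept. Rows 11 to 10 (45 mg, evening 0.15 ml kept) and 14 to 13 (65 mg, evening 0.20 ml kept) behave alike. On these days the evening dose itself had just been raised.

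**Step 5: test the repair.** Go back to the row before the row whose increase was the last one taken before onset.
- Day 6 before the late-evening dose: the last increase was row 5's, so row 4 is held: 20 - 15 = 5 mg lower.
- Overnight after day 6: the last increase was row 6's, so row 5 is held: 25 - 20 = 5 mg lower.
- Day 7 after the morning dose: the last increase was row 7's, so row 6 is held: 30 - 25 = 5 mg lower, as under the onset-day reading.

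Across rows 3 to 12 the reduction is 5 mg after each of the 37 administrations. On row 13 it is 5 mg after three doses and 10 mg after the last, because that row contains two increases.

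**The case against.** The strongest defence is that the rule is clear enough. Section 6.6 reduces the dose administered by one day, and 1.3 and 13.1 speak of one step or the previous step, so the natural reference is the row of the onset day. On that reading the scheduled daily total falls by 5 or 10 mg for every onset from day 3 to day 14. This stands as a statement about row totals. It does not answer onset partway through a day, or overnight, when the participant has not taken the row that is being stepped back from.

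A reader might infer a wider ambiguity from the logbook in 8.3.1, which has "a checkbox ticked by the participant indicating the day of titration that was completed", and conclude that the step-back could equally be counted from the last completed row. The documents do not support that. The checkbox is a data item, and nothing in 6.6 ties the dosing rule to it.

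On harm, the days 1-2 case is a single 0.05 ml late-evening dose, the lowest in the scheme. The Summary describes side effects as mild and gone within 4-8 hours, 8.4 allows withdrawal at any time, and 9.5 provides a safety board. The dose outcome is descriptive and the primary outcome does not use it. All of this stands and limits the weight of the point.

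Investigator's Brochure 5.3.1 or the participant instructions may settle the floor or the reference row. That cannot be excluded, but the operative rule is the one in 6.6.

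**Conclusion.** The point holds in two parts. For onset on day 1 or 2 it is certain from Table 2: the rule as written cannot lower the dose, and 5 mg THC/day is held and counted as sub-side-effect although it produced the effect. For later onset, on the natural reading, the held dose can equal the dose being taken when the effect began, in the circumstances of steps 3 and 4. That second part rests on measuring the dose at onset over the last four windows. How often either situation would occur cannot be derived from the protocol.

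A reader might go further and infer that anyone with onset on days 1-2 must stop the product. The documents do not lead there. The trigger is any self-reported effect, and the list in 8.3.1 includes hunger and dry mouth, which can occur on placebo. Stopping would leave that participant unexposed at the day 14 or day 42 primary measurement in a 16-person crossover. Holding the lowest dose is defensible; labelling it sub-side-effect is not.

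Because the dose endpoint is secondary and descriptive, this is a point to consider and not a threat to the main comparison.

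**What to change.** 1. In 6.6 and the participant instructions, define the step-back as the row before the row whose increase was the last one taken before onset. An effect noticed overnight is then traced to the dose already taken.
2. In 10.2.2, report participants with onset on days 1-2 as having no sub-side-effect dose within the scheme, and list the dose they took separately. Do not enter 5 mg as their maintenance dose. An effect of the day 2 evening dose noticed before the first day 3 dose belongs in the same group. Whether these participants continue at 5 mg or stop is the sponsor's choice, and 6.6 should state it.

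The cost is a sentence or two in 6.6 and the instructions and one in 10.2.2. No visit or assessment is added. The downside is that some participants are held 5 mg THC/day lower than under the onset-day reading.
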